### Secondary objectives

1) To determine whether the PCRM-CI model for persons with hip fracture and CI results in: i) improved mobility at 6 months post-discharge from inpatient rehabilitation; ii) greater improvement in physical functioning at the time of discharge from inpatient rehabilitation and at 6 months post-discharge; iii) a higher proportion of patients returning to their previous living situation in the community at discharge and at 6 months post-discharge.

2) To determine whether the PCMR-CI model results in similar improvements in mobility at discharge from inpatient rehabilitation and 6 months post-discharge for patients with and without CI.

3) To evaluate whether the PCMR-CI model improves HCPs’ attitudes, knowledge, satisfaction, and stress, in caring for patients with CI.

4) To examine the processes by which the PCRM-CI model is implemented by describing: i) the evidence based components of the model that facilities adopt (*i.e.*, how rehabilitation staff in the facilities decide which components they will and can replicate); ii) the context (*i.e.*, evaluation of the preparedness of the context to embrace and sustain implementation); and iii) how the change is facilitated (*i.e.*, how and what supports the unit managers use to introduce, implement and sustain the new model) at the study sites.

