### Sample size

Sample size was determined based on the pilot data on two outcome measures and based on the requirement of the statistical methods that will be used to test the objectives. The primary outcome is the mobility gains score, the difference between mobility scores at discharge and at admission. In the Pilot Project at Toronto Rehab [32], the mean mobility gains score was 12.0 with a standard deviation of 5.7. This effect size was large: 2.1. The mean mobility gains score is expected to be higher for the PCRM-CI group than for the usual care group. If we assume that the mean mobility gains score for the usual care group will be 7.2 and the mean mobility gains score for the PCRM-CI group will be 12.1, with a common standard deviation of 5.7, the sample size estimate is 23 patients with an alpha of 0.05, power of 80% and a two sided *t*-test. In the Pilot Project, a secondary outcome was the rate of return to the community, which was 80% for patients with CI, and the PCRM-CI group is expected to maintain this rate. One can estimate that the rate of return to the community in the Usual Care group is about 50%. For comparison of these two proportions, with an alpha of 0.05 and power at 80%, the sample size estimate is 39 patients for each of the Usual Care and PCRM-CI groups. In order to allow for attrition, our goal will be to recruit additional patients beyond the minimums for a sample size of 140 patients (70 patients in each cohort).

Previous recruitment rates for evaluation studies have indicated that most staff are willing to participate. A sample size of 35 staff was estimated as sufficient to demonstrate changes in HCPs’ attitudes, based on results from the pilot project.

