### Data analysis

Objective #1: The primary objective is to determine the impact of PCRM-CI on improvements in mobility (FIM locomotion and mobility) at discharge. At each site and for Usual Care and PCRM-CI groups, mobility is to be assessed at entry into rehab and at discharge from rehab. The change scores for patient outcomes will be compared with paired t-tests by cohort and site. In secondary analyses, multivariate regression will be used to examine the independent effects of each independent variable of interest on patient outcomes while controlling for other predictors and patient baseline factors**.**

Objective #2 (1 & 2): In the second instance, the mobility and physical functioning change scores and return to prior residence for Usual Care patients will be compared to those for PCRM-CI patients to assess the relative impact of the PCRM-CI model on outcomes for each site. Cross tabulations will be employed to assess rates of return to residence by rehab program and site. In particular, patients with CI are to be specifically targeted in the PCRM-CI model. We will compare means of mobility and physical functioning gains scores for patients with and without CI by program and site to assess the relative impact of the PCRM-CI model on patients with CI. In secondary analyses, multivariate regression will be used to examine the independent effects of each independent variable of interest on patient outcomes while controlling for other predictors and patient baseline factors**.**

Objective #2 (3): The introduction of the PCRM-CI model on the two units is meant to a) improve HCPs’ knowledge and attitudes toward working with hip fracture patients with CI, and b) measure the impact on provider satisfaction and work stress of working with these patients.

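### Secondary objective 2 asks whether mobility gains are similar with and without CI, but the analyses named for it cannot support a similarity conclusion, and splitting by site makes a real difference easier to miss

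*Protocol article*

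**What the plan says.** The protocol article, Secondary objectives, item 2, sets out to determine whether the model "results in similar improvements in mobility at discharge from inpatient rehabilitation and 6 months post-discharge for patients with and without CI".

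The Data analysis section, under Objective #2 (1 & 2), gives the matching analysis: "We will compare means of mobility and physical functioning gains scores for patients with and without CI by program and site". Its stated purpose is "to assess the relative impact of the PCRM-CI model on patients with CI". The same paragraph adds that, in secondary analyses, "multivariate regression will be used to examine the independent effects of each independent variable of interest on patient outcomes", with adjustment for other predictors and baseline factors.

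The Sample size section covers only usual care against PCRM-CI. It takes 7.2 points as the average gain under usual care; for the other cohort it assumes that "the mean mobility gains score for the PCRM-CI group will be 12.1, with a common standard deviation of 5.7". It gives no number for the comparison of patients with and without CI.

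**The concern.** The objective is a question about similarity, and the named analyses address a question about difference. A comparison of means that finds no clear difference may reflect similar gains or too few patients, and nothing in the described analysis separates the two. Splitting by program and by site shrinks the groups, so a real shortfall in patients with CI becomes easier to miss.

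Access to rehabilitation for patients with CI is the study's rationale (Background and Discussion), and admission criteria were widened to take more of them (Data collection). A statement that they gain as much as other patients would interest policy makers, so it should not be easier to reach in a smaller or more finely divided sample.

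**Working it through.** **Inputs**
- SD of the mobility gain 5.7; planned gains 7.2 and 12.1, a difference of 4.9 (Sample size).
- 70 patients per cohort (Sample size); two sites (Methods/Design).
- Share with CI: assumed 31% to 65%, the article's figure for older orthopedic patients (Background). The share actually admitted may differ.
- Site split: assumed equal, 35 patients each. The article does not state it.
- SD assumed the same with and without CI, with no covariate adjustment.

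**1. The plan's own figure.** With the normal approximation, n = 2 × [5.7 × (1.960 + 0.842) / 4.9]² = 21.2, so 22 per group. The exact two-sided *t*-test gives 22.24, so 23 per group. The stated 23 reproduces as a per-group number for usual care against PCRM-CI.

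**2. Group sizes with and without CI in the PCRM-CI cohort**
- Pooled, 70 patients: 22/48 at 31%, 35/35 at 50%, 46/24 at 65%.
- One site, 35 patients: 11/24, 18/17, 23/12.

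**3. Precision and chance of missing a gap.** SE = 5.7 × √(1/n₁ + 1/n₂). The 95% half-width is *t* × SE, with *t* = 1.995 on 68 degrees of freedom and 2.035 on 33. The chance of a non-significant result comes from the noncentral *t* distribution with noncentrality gap/SE. The 2.45-point gap is half of 4.9 and is illustrative only.

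| Setting | n with/without CI | SE | Half-width | True 2.45 gap non-significant |
|---|---|---|---|---|
| Pooled | 22/48 | 1.47 | 2.93 | 62% |
| Pooled | 35/35 | 1.36 | 2.72 | 57% |
| Pooled | 46/24 | 1.44 | 2.86 | 61% |
| One site | 11/24 | 2.08 | 4.22 | 79% |
| One site | 18/17 | 1.93 | 3.92 | 77% |
| One site | 23/12 | 2.03 | 4.13 | 78% |

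Within one site, even a true gap of 4.9, as large as the whole planned effect, is non-significant 31% to 37% of the time. If enrolment followed the 40 and 20 beds in Setting and sample (47 and 23 patients), the smaller site would miss a 4.9-point gap 50% to 56% of the time.

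**4. Six months.** The Discussion reports an 8% reduction in the control cohort. Applied to this cohort, 70 × 0.92 ≈ 64 patients, and the pooled half-width becomes 2.9 to 3.1.

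**5. What margin could be met?** Suppose similarity is claimed only if the whole 95% interval lies within ±m. With no true difference, the chance of success is the average, over the sampling distribution of the estimated SD *s*, of 2Φ[(m − *t* × *s* × √(1/n₁ + 1/n₂)) / SE] − 1, taken as zero where negative. For 35/35:

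| Margin m | Chance of meeting it |
|---|---|
| 2.7 | 5% |
| 3.5 | 43% |
| 4.4 | 78% |
| 4.9 | 89% |

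A margin near the half-width of 2.72 almost always fails, because the interval fits only when the observed difference is close to zero and *s* is a little low. With the uneven splits, the chance at 4.9 falls to 82% to 84%.

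**The case against.** **No decision rule is written.** A reader might infer that the investigators will take a non-significant difference as proof of similarity. The article does not say so. It names no significance test for this comparison, and its stated purpose of assessing relative impact can be read as descriptive estimation. This objection stands.

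**The margin may be in a document not shown.** A numerical limit for a secondary objective is something an article commonly leaves to the full protocol or analysis plan. Its absence alone is therefore no finding. What remains is a mismatch between two statements that the article does make: an objective about similarity and analyses that address difference.

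**Means are not the only analysis.** Adjusted regression is planned, and cognition and delirium are among the measured patient factors. It would be wrong to say that the plan stops at means. But the regression is described as estimating independent effects and is not directed at similarity.

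**The numbers rest on assumptions.** Neither the CI share nor the site split is given, and 4.9 is the gap planned between programs, not a tolerance between patients with and without CI. So 2.45 has no standing as a limit. Across the assumed range of CI shares, however, the picture does not change, and unequal sites make the smaller site worse.

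**The main claim does not need parity.** The primary objective and the Discussion's hypothesis concern improvement in patients with CI, whatever others gain. That limits the weight of this point but does not remove it.

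**Conclusion.** The point holds as a mismatch between objective and analysis. The article asks whether gains are similar with and without CI, and the comparison of means and secondary regression named for that question cannot, as described, support a yes. The by-site split weakens them further. With SD 5.7, 70 PCRM-CI patients and 31% to 65% with CI, the half-width is about 2.7 to 2.9 points pooled and 3.9 to 4.2 per site with equal enrolment. A 2.45-point gap, used only as an example, would be non-significant 57% to 62% and 77% to 79% of the time. These are unadjusted figures; adjustment for admission score could improve precision by an amount the article does not allow one to compute.

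It does not follow that the investigators intend to equate non-significance with similarity, or that the primary conclusion is affected. This is a secondary objective that should be corrected.

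**What to change.** In Data analysis, Objective #2 (1 & 2):

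1. Estimate the CI minus non-CI difference in mobility gain within the PCRM-CI cohort, pooled over sites, with site and admission FIMM as covariates, at discharge and at 6 months.
2. Report it with its 95% confidence interval, alongside the cohort-by-CI interaction. Keep by-site results as description.
3. State that a non-significant difference will not be read as similarity.
4. Claim similarity only if the 95% interval lies inside a clinically justified margin, fixed before PCRM-CI outcomes are examined.
5. If no margin of about 4.4 points or more can be justified, reword secondary objective 2 as estimating the difference in gains. A margin of that size is close to the whole planned effect of 4.9, so rewording may well be the realistic choice.

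The cost is a change of wording, with no new patients or measurements. The downside is that the similarity claim becomes harder to make.

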## Discussion

In most rehabilitation facilities, CI makes patients ineligible for admission to rehabilitation. This leads to huge costs to the health care system as many of these patients await placement in acute care beds, become institutionalized, and within a year are immobile [15,19,58]. Based on results from our pilot work, we hypothesize that the PCRM-CI model can improve the mobility and functional outcomes of clients with CI, and allow them to return home at their prior level of function. This controlled study will provide evidence of the clinical effectiveness of this model. This demonstration project will also allow us to study the contextual factors important for understanding the transferability of the model into other jurisdictions, beyond academic teaching facilities. Study results will provide decision and policy makers with practical knowledge on models of care for persons with a hip fracture who have CI.

The study is critical given the increasing number of elderly persons with hip fractures, as it will contribute to meeting the emerging health needs of the population by improving the provision of services for elders with CI. Progress to date includes the collection of data on all 70 control subjects. At 6 months our sample was reduced by 8% due to attrition and mortality. Forty-five intervention subjects are enrolled with an end date of March 2012. From both facilities 65 health care professionals have agreed to participate in the study and have completed questionnaires at time 1 with the time 2 data to be completed at the end date.

Implementation of the model of care is timely, as the population is aging and the number of individuals with hip fracture and cognitive impairment is increasing. Sustainability after the life of the research project will be achieved by mentoring a staff person to be a ‘clinical coach’, *i.e.*, a future resource. If this rehabilitation model of care proves successful at the two study sites, there will be resources dedicated to implement the model of care into other rehabilitation facilities in its catchment area. This will likely also influence the practices of other hospitals, in keeping with their commitment to seniors’ care.

Given our extensive inclusion criteria and our partnering with community-based facilities, we anticipate that our study results can be generalized to hip fracture patients nationally and internationally. Hence, this study is timely and relevant to policy makers, health care administrators and providers, and the public.
